## 5.4 SAFETY MONITORING

The Protocol Safety Review Team (PSRT) (see **Section 8.8**), will have the primary responsibility for the real-time oversight of safety data, SAE reviews and study pause reviews.

# 6 STATISTICAL CONSIDERATIONS AND SAMPLE ANALYSIS

## 6.1 OVERVIEW

This study is a multi-center trial to assess the safety and immunogenicity of prime-boost vaccination regimens with the investigational plasmid HA DNA vaccine directed towards the 2012/13 influenza vaccine strains as a prime followed 16 weeks later by the 2012/13 influenza TIV or ATIV boost (AGRIFLU or FLUAD, respectively) as compared to the respective single injection of TIV or ATIV. The study will also evaluate the safety and immunogenicity of vaccination regimens with concurrent administration of 2012/13 HA DNA vaccine and TIV or ATIV followed by administration of the subsequent season (2013/14) TIV or ATIV 40 weeks later.

## 6.2 OBJECTIVES

The primary safety objectives relate to the safety and tolerability of each vaccination regimen. The primary immunogenicity objective is to compare the HAI response from the same season prime-boost regimens (2012/13 HA DNA prime and TIV or ATIV boost with a 16 week interval) measured 3 weeks following the boost injection, with the HAI response at three weeks following TIV or ATIV alone. The secondary immunogenicity objectives are to evaluate the HAI and neutralizing antibodies for all vaccine regimens three weeks after each injection.

## 6.3 ENDPOINTS

### 6.3.1 Primary Endpoints: Safety

Assessment of product safety will include clinical observation and monitoring of hematological parameters. Safety will be closely monitored after each injection and evaluated by clinical visits through 24 weeks after the boost injection on each schedule. The following safety endpoints will be assessed for all Study Groups:

- Occurrence of solicited local reactogenicity signs and symptoms for 7 days following each vaccination
- Occurrence of solicited systemic reactogenicity signs and symptoms for 7 days following each vaccination
- Mean change from baseline for safety laboratory measures at week 3 and day of the boost
- Occurrence of adverse events of all severities through 28 days after the prime injection and through 28 days after TIV or ATIV boost
- Occurrence of serious adverse events through last study visit
- Occurrence of Influenza or influenza-like illness events through last study visit

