## 4.2 STUDY SCHEDULES

The study schema is shown in Table 4.1 and the study schedules that apply to study Groups are in **Appendix III**. Schedule A applies to Groups 1 and 2, while Schedule B applies to Groups 3, 4, 5 and 6. After Day 0, deviations from the visit windows in completing study visits are discouraged and will be recorded as protocol deviations, but are permitted, at the discretion of the Investigator of Record (IoR) or designee in the interest of obtaining subject safety and immunogenicity evaluations following study vaccinations.

During or following any visit, if there is any concern about the well-being of the subject, the clinical study site will conduct appropriate medical evaluations by history, physical, laboratory or other indicated testing.

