#### 6.5.3 Safety Analysis

**Reactogenicity:** The number and percentage of subjects experiencing each type of reactogenicity sign or symptom will be tabulated by severity. For a given sign or symptom, each subject's reactogenicity will be counted once under the maximum severity for all assessments.

**Adverse Events:** Adverse Events (AEs) will be coded into Medical Dictionary for Regulatory Activities (MedDRA) preferred terms. The number and percentage of subjects experiencing each specific adverse event will be tabulated by severity and relationship to study product. For the calculations in these tables, each subject's adverse event will be counted once under the maximum severity or strongest recorded causal relationship to study product.

A complete listing of AEs for each subject will provide details including severity, relationship to study product, onset, duration and outcome.

**Safety Laboratory Values:** Safety laboratory values will be summarized as the mean change from baseline along with 95% confidence interval at each timepoint measured in the study. Boxplots of safety laboratory values will be generated for baseline values and for values measured during the course of the study.

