| Medical history targeted to eligibility at screen; interim history for AEs other visits            |      | X               | X                                                       |          | X          | X          |          | X          | X          |
|  Study Vaccinations                                                                    |      |                 | X                                                       |          |            | X          |          |            |            |
| Begin 7-Day Diary Card                                                                             |      |                 | X                                                       |          |            | X          |          |            |            |
| Telephone contact; clinic visit if indicated                                                       |      |                 |                                                         | X        |            |            | X        |            |            |
| Counseling on pregnancy prevention                                                                 |      |                 | X                                                       |          | X          |            |          |            |            |
| CBC, platelets                                                                                     | EDTA | 3               | 3                                                       |          | 3          |            |          |            |            |
|  Pregnancy test: urine (or serum)                                                      |      | X               | X                                                       |          | X          | X          |          |            |            |
| Creatinine and ALT                                                                                 | SST  | 4               |                                                         |          |            |            |          |            |            |
| Research Immunology                                                                         |      |                 |                                                         |          |            |            |          |            |            |

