| Antibody assays and serum storage                                                                  | SST  | 16  | 24                                                      |          | 32         | 32         |          | 32         | 32         |
| PBMC and plasma for storage                                                                        | EDTA | 40  | 80                                                      |          | 60         | 60         |          | 60         | 60         |
| Daily Volume (mL)                                                                           |      | 63       | 107                                              | - | 95  | 92  | - | 92  | 92  |
| Max. Cumulative Volume (mL)                                                                 |      | 63       | 170                                              | - | 265 | 357 | - | 449 | 541 |

 Screening informed consent may be signed more than 8 weeks prior to study enrollment; screening evaluations may be repeated, if needed.

The screening blood draw for research does not need to be repeated if it was collected more than 70 days prior to enrollment. Day 0=day of enrollment and HA DNA vaccine injection. Day 0 evaluations prior to first injection are the baseline for assessing adverse events subsequently.

 Complete post vaccination evaluations (BP, pulse and injection site assessment) at 15-60 minutes after study injections.

 Negative pregnancy test results must be confirmed for women of reproductive potential prior to administering each injection. TIV is not contraindicated for pregnant women, but the woman must be informed of result prior to administering TIV as part of this research protocol. If pregnant, research blood draws will be one-fourth of shown volume or eliminated if the pregnant participant is anemic.

**Visit windows:** Schedule Visits 02A through 05 with respect to Day 0; the following visit windows apply: 02A(+4 days); Visits 03(+7 days); Visit 05 (+14 days). Schedule Visits 05A through 07 with respect to actual Visit 05 date; the following windows apply: 05A(+4 days); Visits 06 (+7 days), visit 07 (±7 day window). The schedule for Groups 1 and 2 does not include a “visit 04”.

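### A primary safety endpoint calls for a laboratory value on the day of the boost, but neither visit schedule draws a safety laboratory sample at that visit

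*Protocol*

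**What the plan says.** Section 6.3.1 introduces its list with "The following safety endpoints will be assessed for all Study Groups", so each item applies to Groups 1 to 6. The third of its six items is "Mean change from baseline for safety laboratory measures at week 3 and day of the boost". The same section describes the laboratory part of the safety assessment as "monitoring of hematological parameters".

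Appendix III gives the samples in two tables, Schedule A for Groups 1 and 2 and Schedule B for Groups 3 to 6:

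- The row "CBC, platelets" shows 3 mL at screening, Day 0 and Week 3 in both schedules, and nothing at the boost visit or later.
- The row "Creatinine and ALT" shows 4 mL at screening only.
- At the boost visit the tubes are 32 mL for antibody assays and serum storage, and 60 mL in the row "PBMC and plasma for storage". A pregnancy test is also scheduled there.

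Section 6.5.3 states the analysis: "Safety laboratory values will be summarized as the mean change from baseline along with 95% confidence interval at each timepoint measured in the study". Section 4.2 provides for additional testing at any visit, on the condition "if there is any concern about the well-being of the subject, the clinical study site will conduct appropriate medical evaluations by history, physical, laboratory".

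**The concern.** The endpoint section promises a group mean change at a visit where the schedule provides nothing to measure it with. Sites draw blood according to Appendix III, so the gap would show only at analysis, when the samples could no longer be obtained. The report would then have to leave out one of the two stated time points of a primary safety endpoint, with no prior explanation in the protocol. A statistical analysis plan cannot repair this, because it cannot supply values from samples that were never drawn. Both the endpoint and the schedule are explicit protocol content, so this is a contradiction and not detail left for later.

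**Working it through.** The question is whether the blank cells at the boost visit are real or were lost when the tables were read from PDF. The stated blood volumes answer it.

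**Inputs** (Appendix III, both schedules): blood count 3 mL; creatinine and ALT 4 mL; serum tubes 16, 24 or 32 mL; research EDTA tubes 40, 80 or 60 mL; and the stated daily and cumulative volumes.

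**Formula:** daily volume = blood count + chemistry + serum tubes + research EDTA tubes.

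| Visit | Sum (mL) | Stated (mL) |
|---|---|---|
| Screening, A and B | 3 + 4 + 16 + 40 = 63 | 63 |
| Day 0, A and B | 3 + 0 + 24 + 80 = 107 | 107 |
| Week 3, A and B | 3 + 0 + 32 + 60 = 95 | 95 |
| Week 16, B (no vaccination) | 0 + 0 + 32 + 60 = 92 | 92 |
| **Boost: Week 16 in A, Week 44 in B** | **0 + 0 + 32 + 60 = 92** | **92** |
| Weeks 19 and 40 in A; Weeks 47 and 68 in B | 0 + 0 + 32 + 60 = 92 each | 92 each |

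**Cumulative totals:**

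- Schedule A: 63 + 107 + 95 + 92 + 92 + 92 = 541 mL, as stated.
- Schedule B: 63 + 107 + 95 + 92 + 92 + 92 + 92 = 633 mL, as stated.

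All 13 visit totals (6 in A, 7 in B) and all running totals reproduce exactly. The research tubes account for the whole boost-visit volume: 92 − 32 − 60 = 0 mL is left for safety tests. A 3 mL blood count there would have given 95 mL for the visit and 544 mL (A) or 636 mL (B) at the end. The blank cells are therefore genuine.

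**Other possible sources of a boost-day value:**

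- The pregnancy test is qualitative and gives no mean change.
- The 60 mL of EDTA blood is assigned to research storage, not to a blood count.
- Testing under Section 4.2 depends on a clinical concern. It would cover a selected subset and could not stand for the group mean.
- Section 6.5.3 summarises what is measured and adds no sample.

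**Result:** scheduled boost-day safety laboratory values exist for 0 of 110 subjects in Groups 1 and 2 (2 × 55) and 0 of 220 in Groups 3 to 6 (4 × 55), that is 0 of 330. The Week 3 change can be computed for blood count and platelets, which have Day 0 and Week 3 samples. Creatinine and ALT have no scheduled value after screening, so no change can be computed for them if they are meant to be covered.

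**The case against.** The best defence is that this is a slip of wording with little consequence. The analysis text in Section 6.5.3 follows whatever time points are measured, so it already fits the schedule, and only the endpoint item is out of step. The gap concerns one of two time points in one of six safety items; reactogenicity, adverse events, serious adverse events and influenza illness do not depend on it. The pause rule in Section 4.5 turns on related Grade 4 or 5 events, not on mean laboratory change, and Section 6.4 says that no formal superiority or non-inferiority hypothesis is tested. All of this is correct and limits the weight of the point. It does not remove the contradiction, because Section 6.3.1 still names a boost-day value as primary.

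A reader might also infer more than the documents support:

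- *That there is no haematology before the boost.* Screening, Day 0 and Week 3 blood counts all precede it. What is missing is any scheduled blood count on the boost day.
- *That the lack of chemistry or haematology after vaccination or boost breaks a promise.* Section 6.3.1 speaks of haematology and asks for Week 3 and the boost day only. Creatinine and ALT are eligibility criteria in Section 4.1.1. In Groups 3 to 6, moreover, the Week 3 blood count does follow TIV or ATIV, given alone or with HA DNA.
- *That no subject could have any boost-day value.* Section 4.2 allows unscheduled tests, so the count of zero refers to scheduled values.

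**Conclusion.** The contradiction stands in this limited form. Followed exactly, the protocol leaves one of the two time points of a primary safety endpoint without scheduled data in all six groups, and that half of the endpoint cannot be computed. The other half can be, for blood count and platelets.

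The conclusion rests on Appendix III being the complete list of planned samples, which its own volume totals support, and on enrolment as planned at 55 per group. It is an inconsistency to correct before enrolment. It does not threaten the other safety endpoints or the immunogenicity comparisons, and it is not evidence that laboratory monitoring before the boost is absent.

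**What to change.** Reconcile Section 6.3.1 with Appendix III in one of two ways; which one was intended is for the sponsor to decide.

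1. Remove the boost-day time point from the laboratory endpoint, leaving Week 3. This is a wording change and alters no blood volume.
2. Schedule the blood count at Visit 05 in both schedules. This adds one 3 mL tube at an existing draw: 92 + 3 = 95 mL at that visit, with final cumulative totals of 541 + 3 = 544 mL (A) and 633 + 3 = 636 mL (B). The running totals from Visit 05 onward need the same 3 mL.

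In either case, state in Section 6.3.1 that the safety laboratory measures are blood count and platelets, so that creatinine and ALT are not read into an endpoint for which they have no later sample.

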|       |          | 5b: 51-70 years                                                                                                                                                                                                                                           |                           |                                       |                            |
| 6     | 55       | 6a: 18-50 years                                                                                                                                                                                                                                           |                           | HA DNA (left arm)
TIV (right arm)  | TIV                        |
|       |          | 6b: 51-70 years                                                                                                                                                                                                                                           |                           |                                       |                            |
| Total | 330      | * May be delayed pending TIV/ATIV availability.
All vaccinations are open-label and intramuscular (IM) in the deltoid.
HA DNA injections will be administered via Biojector.
ATIV and TIV injections will be administered by needle and syringe. |                           |                                       |                            |

The randomization to Groups 1 and 2 will occur first. Once these groups are filled, randomization to Groups 3-6 will occur. Randomizations are stratified by age, subgroups “a” includes subjects 18-50 years of age and subgroups “b” includes subjects 51-70 years of age, in order to keep similar age distribution to the groups.

**Study Duration:** Subjects will be evaluated for safety and immune responses throughout the trial for 24 weeks following the boost. Duration of time on study will be 40 weeks for Groups 1 and 2 and 68 weeks for Groups 3, 4, 5 and 6.

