In this study, we are evaluating the safety and immunogenicity of same season and sequential season vaccination schedules. The same season regimens (2012/13 prime and boost with a 16 week interval) consist of HA DNA prime with ATIV boost -- or -- HA DNA prime with TIV boost; the active comparator for these regimens will be ATIV or TIV alone because this is the standard for adult influenza vaccination within a single season. The sequential season regimens (2012/13 prime and 2013/14 boost with a 44 week interval) consist of concurrent administration (in different arms) of HA DNA and ATIV prime with ATIV boost -- or -- HA DNA and TIV prime with TIV boost; the active comparator for these regimens will be ATIV followed by ATIV boost or TIV followed by TIV boost, also at a 44 week interval, because this is a vaccination pattern consistent with sequential season vaccinations. Evaluation of these investigational schedules and active comparator schedules will inform development of novel influenza vaccine strategies that may offer improved and cross-protective immunity against antigenically diverse influenza strains.

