| 5     | 55       | 5a: 18-50 years                                                                                                                                                                                                                                           |                           | HA DNA (left arm)
ATIV (right arm) | ATIV                       |
|       |          | 5b: 51-70 years                                                                                                                                                                                                                                           |                           |                                       |                            |
| 6     | 55       | 6a: 18-50 years                                                                                                                                                                                                                                           |                           | HA DNA (left arm)
TIV (right arm)  | TIV                        |
|       |          | 6b: 51-70 years                                                                                                                                                                                                                                           |                           |                                       |                            |
| Total | 330      | * May be delayed pending TIV/ATIV availability.
All vaccinations are open-label and intramuscular (IM) in the deltoid.
HA DNA injections will be administered via Biojector.
ATIV and TIV injections will be administered by needle and syringe. |                           |                                       |                            |

The expected duration of time on study per subject is approximately 40 weeks for Groups 1-2 and 64 weeks for Groups 3-6.

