##### 4.1.1 Inclusion Criteria

*A subject must meet all of the following criteria:*

1. 18 to 70 years old

2. Available for clinical follow-up through Study Week 40 for Groups 1-2 and through Study Week 64 for Groups 3-6
3. Able and willing to complete the informed consent process
4. Willing to donate blood for sample storage to be used for future research
5. Physical examination and laboratory results without clinically significant findings and a Body Mass Index (BMI)  $\leq 40$  within the 70 days prior to enrollment
6. Has not yet received the current year (2012/13) influenza vaccine prior to enrollment and agrees to receive seasonal influenza vaccines during study participation only from the study site

*Laboratory Criteria within 70 days prior to enrollment:*

7. Hemoglobin within institutional normal limits
8. White blood cells either within institutional normal range or accompanied by site physician approval as consistent with healthy adult status
9. Platelets = 125,000 – 500,000/mm^3
10. Alanine aminotransferase (ALT)  $\leq 2.5$  x upper limit of normal (ULN)
11. Serum creatinine  $\leq 1$  x ULN based on site institutional normal range

*Criteria applicable to women of childbearing potential:*

12. Negative human chorionic gonadotropin ( $\beta$ -HCG) pregnancy test (urine or serum) on day of enrollment
13. Agree to use an effective means of birth control from 21 days prior to enrollment through 3 weeks after the second study vaccination

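### SAEs and influenza/ILI are counted over 40 weeks in Groups 1–2 but 68 weeks, including a second TIV/ATIV injection, in Groups 3–4, so their raw frequencies are not like-for-like across schedules

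*Protocol*

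**What the plan says.** Section 6.3.1 lists six primary safety endpoints and applies them to every group. Two (solicited local and systemic reactions) cover 7 days after each vaccination, one (all adverse events) covers 28 days after each injection, and one (laboratory change) is tied to set visits. The other two, SAEs and influenza/ILI, are open-ended; the influenza one is worded "Occurrence of Influenza or influenza-like illness events through last study visit". The same section says that safety is "evaluated by clinical visits through 24 weeks after the boost injection on each schedule".

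The length of follow-up is stated in more than one way:

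- The Précis says: "Duration of time on study will be 40 weeks for Groups 1 and 2 and 68 weeks for Groups 3, 4, 5 and 6". Appendix III agrees, with the last visit at Week 40 (Day 280) in Schedule A and Week 68 (Day 476) in Schedule B.
- The text under Table 4-1 in Section 4 gives "approximately 40 weeks for Groups 1-2 and 64 weeks for Groups 3-6", and the second inclusion criterion in Section 4.1.1 asks for availability "through Study Week 64 for Groups 3-6".
- Section 1 puts the sequential-season boost at 44 weeks. Section 6.1 puts it at 40 weeks for the concurrent regimens.

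Section 6.1 describes the trial as assessing safety and immunogenicity of the HA DNA prime-boost regimens against one injection of TIV or ATIV. Section 1 names ATIV or TIV alone as their active comparator. On analysis, Section 6.5.3 says: "The number and percentage of subjects experiencing each specific adverse event will be tabulated by severity and relationship to study product". Section 5.1.2 sends influenza and ILI to a separate form instead of the adverse event form, and Section 6.5.3 gives no summary measure for them.

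**The concern.** Only Groups 3 and 4 can supply the comparator of ATIV or TIV alone. For immunogenicity, Section 6.3.2 handles this well: it reads Groups 3 and 4 three weeks after their first injection, before the second-season dose. The two open-ended safety endpoints have no such cut. Counted to the final visit, Groups 3–4 include a second TIV or ATIV injection, the 24 weeks after it, and part of the 2013/14 season.

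A table that sets these counts beside those of Groups 1–2 mixes the effect of the regimen with length of observation, number of inactivated-vaccine injections and calendar season. If weekly risk were the same everywhere, the comparator would show more events. That would flatter the DNA prime-boost groups, or could hide a modest excess in them.

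**Working it through.** **Follow-up, reproduced.** Duration = prime-boost interval + 24 weeks.

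- Groups 1–2: 16 + 24 = 40 weeks; 280/7 = 40.
- Groups 3–6 with the 44-week interval: 44 + 24 = 68 weeks; 476/7 = 68. The Précis figure is reproduced.
- Groups 3–6 with the 40-week interval of Section 6.1: 40 + 24 = 64 weeks, the figure in Sections 4 and 4.1.1.

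The ratio to Groups 1–2 is 68/40 = 1.7, or 64/40 = 1.6. The extra time is 28 or 24 weeks.

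**Calendar, on projected dates.** Groups 1–2 starting 1–31 August 2012 finish 280 days later, 8 May to 7 June 2013. Groups 3–6 starting 1 October to 30 November 2012 finish 476 days later, 20 January to 21 March 2014. The second season is therefore entered but not necessarily completed.

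**Effect of length alone.** The protocol gives no SAE or influenza rate for this trial, so the 40-week risk p is an assumption, shown over a range. With the same constant weekly risk in all groups, the risk over longer follow-up is q = 1 − (1 − p)^f, with f = 1.6 or 1.7. The last column uses f = 2, meaning two full seasons of equal risk.

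| Assumed 40-week risk | 64 weeks (f = 1.6) | 68 weeks (f = 1.7) | Expected subjects of 55: 40 vs 68 weeks | Upper bound (f = 2) |
|---|---|---|---|---|
| 1% | 1.6% | 1.7% | 0.55 vs 0.93 | 2.0% |
| 2% | 3.2% | 3.4% | 1.10 vs 1.86 | 4.0% |
| 5% | 7.9% | 8.4% | 2.75 vs 4.59 | 9.8% |
| 10% | 15.5% | 16.4% | 5.50 vs 9.02 | 19.0% |
| 20% | 30.0% | 31.6% | 11.00 vs 17.36 | 36.0% |

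**How often this would look like a difference.** The protocol plans no such test. As a yardstick only, take a two-sided 5% Fisher exact test on 55 vs 55 (Group 1 vs Group 3, say) with no true difference in weekly risk. Moving from equal follow-up to 40 vs 68 weeks changes the rejection probability from 0.9% to 3.9% at p = 5%, from 2.0% to 10.1% at p = 10%, and from 2.7% to 21.7% at p = 20%. At p = 1–2%, an assumed SAE range, it stays at or below 0.4%. Pooling 110 vs 220 at 1–2% keeps it below 5%.

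**A window that fits the stated comparator.** Take 24 weeks from the first ATIV or TIV injection: Weeks 16–40 in Groups 1–2, Weeks 0–24 in Groups 3–4. Each side then has one inactivated-vaccine injection and 24 weeks. On projected dates the windows run from 21 November–21 December 2012 to 8 May–7 June 2013, and from 1 October–30 November 2012 to 18 March–17 May 2013. Earliest starts differ by 51 days (about 7 weeks), latest starts by 21 days (3 weeks), and the widest gap, 1 October to 21 December, is 81 days (between 11 and 12 weeks).

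**The case against.** The strongest reply is that no planned analysis is shown to be wrong. The safety objectives in Section 3.1 are to evaluate each schedule and the concurrent injections. Section 6.4.1 gives safety sensitivity within a group of 55. Section 6.5.3 is descriptive and names no contrast. Section 6.4 disclaims a formal superiority or non-inferiority hypothesis. The between-group comparisons that are spelled out concern immune responses. Following everyone for 24 weeks after the boost is an openly stated design choice, and person-time tables often sit in the SAP, which is not at hand.

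Most of this stands, and it limits the point. A reader might infer that the protocol plans an invalid test of safety between schedules; it does not. A reader might also infer that influenza/ILI percentages are planned and would roughly double. The percentage wording covers adverse events, hence SAEs, and no measure is stated for influenza/ILI. Doubling needs two complete seasons of equal risk, whereas the second is only partly covered. Four of the six endpoints are untouched. Comparisons within a schedule (1 vs 2, or among 3–6) have equal follow-up.

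What does not stand is that the matter belongs wholly to the SAP. The counting window is fixed in the protocol's own endpoint definition, and Section 6.1 names safety relative to one TIV or ATIV injection as part of the trial's purpose. A descriptive comparison also needs matching windows.

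**Conclusion.** The point holds as a modest, inexpensive improvement. For SAEs and influenza/ILI, occurrence to the final visit covers 1.6 to 1.7 times as long in Groups 3–4 as in Groups 1–2, plus a second TIV or ATIV injection and part of a second season. It does not match the comparator named in Section 6.1.

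Under equal and constant weekly risk, an assumed 40-week risk of 5% or 10% appears as about 8% or 16%. At an assumed SAE risk of 1–2% the gap is less than one subject in 55, so the practical weight falls on influenza/ILI. All event risks here are assumptions, and constant weekly risk is only a rough description of influenza; the real size and direction for that endpoint depend on the seasons. The documents do not support a claim that a planned safety conclusion will be biased, because no cross-schedule safety test is planned.

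Separately, the 68-week and 64-week statements, and the 44-week and 40-week intervals, contradict each other and must be reconciled.

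**What to change.** In Sections 6.3.1 and 6.5.3:

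1. Keep full-duration counts by group, and use them for comparisons within a schedule (1 vs 2; among 3–6). Print the follow-up length in the table heading.
2. Add rates per person-time for SAEs and influenza/ILI, and state the summary measure for influenza/ILI.
3. For the descriptive comparison of Groups 1–2 with Groups 3–4, count events with onset 0–24 weeks after the first ATIV or TIV injection (Weeks 16–40 and Weeks 0–24).
4. Show Weeks 0–16 of Groups 1–2, after the DNA prime, next to that comparison so that events after the investigational product are not lost.
5. Reconcile the follow-up and interval statements in the Précis, Sections 1, 4, 4.1.1 and 6.1, and Appendix III.

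The cost is a few extra tables and an onset date on the influenza form. No visit or subject is added. Schedule B has no visit at Week 24, so events in Weeks 16–24 of Groups 3–4 may first be recorded at the next planned visit, at Week 44 in Appendix III, and must be placed by onset date.

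Two limits remain and should be stated with the results. Groups 1–2 and Groups 3–6 are randomized in separate, successive steps, so the comparison is not randomized. The windows are also offset by about 3 to 7 weeks on projected dates, and by 11 to 12 at the extreme. Person-time rates do not remove the season difference either, so influenza/ILI differences across schedules need cautious reading.
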